## Abstract

**Background:**

Several studies suggest that the number of risk factors rather than their nature is key to mental health disorders in childhood.

**Method and design:**

The objective of this multicentre randomized controlled parallel trial (PROBE methodology) is to assess the impact in a multi-risk French urban sample of a home-visiting program targeting child mental health and its major determinants. This paper describes the protocol of this study. In the study, pregnant women were eligible if they were: living in the intervention area; able to speak French, less than 26 years old; having their first child; less than 27 weeks of amenorrhea; and if at least one of the following criteria were true: less than twelve years of education, intending to bring up their child without the presence of the child’s father, and 3) low income. Participants were randomized into either the intervention or the control group. All had access to usual care in mother-child centres and community mental health services free of charge in every neighbourhood. Psychologists conducted all home visits, which were planned on a weekly basis from the 7^th^ month of pregnancy and progressively decreasing in frequency until the child’s second birthday. Principle outcome measures included child mental health at 24 months and two major mediating variables for infant mental health: postnatal maternal depression and the quality of the caring environment. A total of 440 families were recruited, of which a subsample of 120 families received specific attachment and caregiver behaviour assessment. Assessment was conducted by an independent assessment team during home visits and, for the attachment study, in a specifically created Attachment Assessment laboratory.

**Discussion:**

The CAPEDP study is the first large-scale randomised, controlled infant mental health promotion programme to take place in France. A major specificity of the program was that all home visits were conducted by specifically trained, supervised psychologists rather than nurses. Significant challenges included designing a mental health promotion programme targeting vulnerable families within one of the most generous but little assessed health and social care systems in the Western World.

**Trial registration:**

Current Clinical trial number is NCT00392847.

## Background

Infant mental health is a public health priority both internationally [1] and in France [2]. Mental health disorders in childhood have long term consequences throughout the lives of the individuals in question, their families and the social environment as a whole [3]. The prevalence of psychiatric disorders in infants is related to a variety of psychosocial vulnerability factors. More emotional and behavioural disorders are seen in children of young, first-time mothers [4,5]; in infants with low quality of home environment [6,7]; in children of mothers with postnatal depression [8,9] or who have less knowledge of infant development [10], less parenting skills [11] or insightfulness [12]; in children of mothers who smoke [13] or who have other health problems [14]; in situations of psychosocial parental stress [15] or less perceived social support [16]; in children of mothers showing attachment disorganization [17]; in preschoolers whose parents do not live together [18]; and in children of families of low socioeconomic status and educational level [18]. Furthermore, individual vulnerability appears to be linked to the accumulation of vulnerability factors rather than being a direct result of one particular factor [19].

Health promotion approaches have explored various strategies, including actions within educational settings as well as home-visiting programs, widely developed since the using a model developed by David Olds [14,20]. In the USA, services based on these latter programs are today supporting more than 500,000 families [21]. In Europe, they are increasingly being integrated into existing social and health care systems [22-24]. One of the main purposes of home-visiting programs is to act upon the determinants of child mental health, particularly by reducing the impact of social stressors on families [25-28], developing parenting knowledge and skills regarding child development [29] and promoting maternal health [30], for example in areas such as diet, sleep and substance misuse [29]. Typically, families receive home visits from qualified nurses or trained paraprofessionals, often from the communities being served, on a weekly or monthly basis, beginning during pregnancy and ending when the child is between two to five years old [31]. A number of studies have shown home visiting to be an effective strategy for improving child development and parenting in vulnerable families [25-28,32], and reducing the risk of child abuse [28]. However, in recent reviews of these programs, only one in two demonstrate significant and positive impacts on children [24,33], a phenomenon often attributed to variation in implementation practices [33,34], to difficulties engaging families [35] or to using home-visiting personnel who are insufficiently trained [30].

The CAPEDP (Compétences parentales et Attachement dans la Petite Enfance: Diminution des risques lies aux troubles de santé mentale et Promotion de la résilience - Parental Skills and Attachment in Early Childhood: reduction of risks linked to mental health problems and promotion of resilience) study is the first randomized, controlled trial assessing an evidence-based, home-visiting program in France. Towards the end of the 1990s, despite the existence in every neighborhood of government-run mother-child services as well as community mental health services for both children and adults, mental health professionals had been becoming increasingly concerned by the number of children living in vulnerable social situations being referred for care, typically for behavioural problems. An international conference [36] confronting evidence-based preventive programs from different national contexts provided the impetus for developing the first French home-visiting program specifically targeting infant mental health, in line with international best practice criteria [24,32,37,38], and adapted to the particularities of the French context. The resulting CAPEDP project involved designing, implementing and evaluating an early, long-term, supervised, home-based intervention targeting the determinants of infant mental health in families presenting multiple psychosocial vulnerability factors.

The CAPEDP program has two major specificities with regard to most other home-visiting programs. The first specificity was to address child mental health promotion in families that already have, at least theoretically, free access to one of the most extensive, comprehensive and longstanding social and health care systems in the Western World. Indeed, at the close of World War II, France developed nation-wide, community-based, mother-child support and prevention services with no out-of-pocket payment, known as the *Protection Maternelle et Infantile* (Mother and Child Protection Services or PMI). Today, mothers have direct access to PMI centres free of charge from the beginning of pregnancy right through to their child’s third birthday. France was also the first Western country to develop, across the country, free community mental health services for both adults and children. With regard to child and adolescent care, each community mental health service provides care with no out-of-pocket payment for a population area of an average 250,000 inhabitants and, although with limited resources, being able provide home visits if deemed necessary for the child’s mental health or safety. Families also automatically access specific social benefits (*allocations familiales*) provided by local government to help raise their children, if they accept to bring them in for a limited number of health check-ups and compulsory vaccinations. Furthermore, families identified by maternity ward staff as being particularly vulnerable will receive home visits by PMI nurses - although a 2002 study revealed that, in the majority of cases (60%), this happened only once and only 7% of these more vulnerable families received more than three home visits [39]. Although PMI nurses receive no specific training on mental health promotion or prevention and little organised psychological supervision, they can and do refer families directly to their local community child and adolescent mental health service. As for the PMI, the functioning, outcomes and cost/efficiency of these mental health services have undergone little systematic evaluation.

The second major specificity of the CAPEDP intervention was that the entire home-visiting program was conducted by qualified psychologists. It was hypothesised that professionals who were more highly trained in psychology would be more competent in recognizing the elements in play with regard to the determinants of infant mental health and more skilled in acting upon these determinants.

### Objectives

The aim of the CAPEDP trial was to evaluate, in young primiparous mothers presenting vulnerability factors associated with greater likelihood of child mental health disorders, the impact on infant mental health of a home-visiting program conducted by trained psychologists and targeting the major modifiable determinants of infant mental health.

The program evaluated three primary outcomes: child mental health at the age of two, as well as two potential mediating variables: maternal postnatal depression at three months postpartum and the quality of the home environment when the child was 12 months old.

Secondary objectives included evaluating the impact of the intervention on: maternal postnatal depression at 6 months postpartum, infant attachment quality at 18 months of age, the mother’s quality of attachment at her child’s second birthday, her knowledge and use of social, medical and educational support services, her perception of receiving support from her own personal network, her parenting perceptions and behaviour, the child’s psychomotor development, sustained withdrawal behaviour of the child at 18 months, the mother’s knowledge concerning child development, her parental stress concerning caring for her child, her access to training and employment, her own psychological health and, in the intervention group, the working alliance between the mother and the home-visiting team (Table 1).

**Table 1 T1:** Outcome criteria and assessment schedule

**Instrument**	**Concept measured**	**Validation**	**Outcome assessor**	**Structure of instrument; scoring**	**Time of measurement**					
			**Place of evaluation**		**Prenatal**	**3 mths after birth**	**6 mths after birth**	**12 mths after birth**	**18 mths after birth**	**24 months after birth**
Edinburgh Post- partum Depression Scale (EPDS)	Pre and pospartum depression	Cox et al., 1987 [40]	Mother during home visits	10 items, 4 point-Likert scales (0–3)	X	X	X	X		
		French validation: Guedeney & Fermanian, 1995 [41]		Range 0–30						
				Higher scores indicate higher levels of depressive symptoms.						
Home Observation for the Measurement of the Environment (HOME) inventory	Quality of the home environment (quality and quantity of stimulation and support available to the child in the home environment)	Bradley & Caldwell, 1979 [42]	Assessment team during home visits	Designed for use during infancy (birth to age three).		X		X	X	
		French validation Gunning et al, 2004 [43]		45 items (yes/no response)						
				Six subscales:						
				Parental Responsitivity (11 items)						
				Acceptance of the child (8 items)						
				Organization of the environment (6 items)						
				Learning Materials (9 items)						
				Parental Involvement (6 items)						
				Variety in Experience (5 items)						
				Highest scores for each subscale indicate greater environment.						
Child Behavior Checklist 1½-5 (CBCL 1½-5)	Child behavioural disorders	Achenbach 2009 [44]	Assessment team during home visits	100 items, Likert scales (0–2)						X
				Range 0–200						
		French validation: Ivanova et al, 2010 [45]								
				A total score and 7 syndrome scales:						
				Emotionally Reactive (0–18, clinical range (CR) >8)						
				Anxious/Depressed (0–16, CR>8)						
				Somatic Complaints (0–22, CR>6)						
				Withdrawn (0–16, CR >5)						
				Sleep Problems (0–14, CR>8)						
				Attention Problems (0–10, CR>6)						
				Aggressive Behaviour (0–38, CR>24)						
Attachment Q –Sort (AQS)	Child’s attachment	Waters & Deane, 1985 [46]	Assessment team during home visits	Two raters assess each situation, during a home visit of two hours.					X	
		French translation made and validated by a panel of infant mental health experts								
				90 items						
				Correlation with typical secure pattern:						
				Insecure attachment if < 0.35						
				Secure attachment if ≥0.35						
Vulnerable Attachment Style Questionnaire (VASQ)	Mother’s attachment	Bifulco et al., 2003 [47]	Mother during home visit	22 items, 5-point Likert scale (1–5).	X					X
				Range 0–110						
				1 global scale: Vulnerability (0–110, vulnerability if ≥ 57)						
				2 sub-scales:						
				Insecurity (range 0–60, insecure if > 30)						
				Proximity seeking (range 0–50, proximity seeking if ≥ 27)						
Services Questionnaire	Use of social and / or medical services	Specifically designed for this research	Assessment team during home visits	Description of the use of 27 social and / or medical services	X	X	X	X		X
Social Support Interview (SS-A; SS-B)	Perception of social support received and level of satisfaction from the social network	Designed for this research based on Vaux, 1988 [48]	Assessment team during home visits	6 items	X	X		X		X
				Description of social support structure (emotional, material, financial, socialization, valorization)						
Parental Cognitions and Conduct Toward the Infant Scale (Pacotis)	Parenting: mother perception of her attitude and behaviour towards her child, of her competence or incompetence and of her emotional investment of the child.	Boivin et al., 2005 [49]	Mother during home visit	17 items, numeral rating scales (0–10)		X		X		
				3 sub-scales (mean score of items)						
				Parental self-efficacy; Perception of parental impact; Hostile-reactive parenting behaviour						
				Higher sub-scale scores indicate lower parental self-efficacy, perception of less parental impact on the child's behaviour, and higher parental use of hostile-reaction behaviour.						
Brunet-Lézine developmental test (BL-Revised)	Child development (0 to 5 years)	Brunet & Lezine, 1965 [50]	Assessment team during home visits	Developmental age (developmental quotient)			X	X		
				4 dimensions:						
				Language						
				Motor gross						
				Motor fine						
				Social relationships						
				30 item test scored partly						
				on observation, partly on questions to parents						
		Original scale in French								
Alarm Baby Distress scale (ADBB)	Sustained withdrawal behaviour	Guedeney & Fermanian, 2001 [51] in France	Assessment team during home visits	8 items, 5-point Likert scale (0–4), Range 0–32					X	
				Withdrawal behaviour if ≥ 5						
Knowledge of Infant Development Inventory (KIDI)	Mother’s knowledge of infant development	McPhee, 1981 [52]	Mother during home visit	48 items (−1, 0, 1)	X	X				X
				Range −48 to 48						
				Highest scores indicate better knowledge.						
Parental Stress Inventory (PSI)	Parental stress	Abidin & Wilfong, 1989 [53]	Mother during home visit	24 items, Likert scales (1–5)		X	X	X		X
				Two subscales (mean score of items):						
				Parental stress						
				Dysfunctional interaction						
				Higher scores indicate greater parental stress.						
Symptom Check-list (SCL-90)	Mother’s psychological disorders	Derogatis, 1994 [54]	Mother during home visits	90 items, 5 point-Likert scales (0–4)	X	X				X
				10 subscales:						
				Somatization (0–48)						
				Obsessive-Compulsive (0–40)						
				Interpersonal Sensitivity (0–36)						
				Depression (0–52)						
				Anxiety (0–40)						
				Hostility (0–24)						
				Phobic Anxiety (0–32)						
				Paranoid Ideation (0–24)						
				Psychoticism (0–40)						
				Other symptoms (0–28)						
				Higher scores indicate greater clinical impairment.						
Working Alliance Inventory (WAI)*	Working alliance between the mother and the CAPEDP intervention psychologist	Horvath & Greenberg, 1989 [55]	Mother during home visits	12 items, Likert scale (1–7)		X	X	X	X	X
				Range 12–84						
		French validation Guedeney et al, 2005 [56]								
				Higher scores indicate better working alliance						
Strange Situation Procedure (SSP)^#^	Infants’ Attachment	Ainsworth & al, 1978 [57]	Assessment team viewing video of infant in attachment laboratory	Categorical				X		
								(12 to 15 mths)		
				Attachment:						
				Secure						
				Insecure-Avoidant						
				Insecure-Ambivalent/Resistant						
				Disorganised/Disoriented						
Atypical Maternal Behaviour Instrument for Assessment and Classification (AMBIANCE) ^#^	Maternal Disruptive Behaviour	Lyons-Ruth, Bronfman, & Parsons, 1999 [58]	Assessment team viewing video of mother in attachment laboratory	Categorical:				X		
				Maternal Affective Communication not Disrupted if < 5				(12 to 15 mths)		
				Maternal Affective Communication Disrupted if ≥ 5						
				2 Sub-styles:						
				Withdrawal /Disoriented						
				Hostile/Role Confusion						
Insightfulness Assessment (IA) ^#^	Maternal Auto-reflexive function	Oppenheim & Koren-Karie 2002 [59]	Assessment team viewing video and interview of mother in Attachment laboratory	10 scales, giving way to a 4 category classification:				X		
								(12 to 15 mths)		
				Positive Insight						
				One-sided						
				Disengaged						
				Mixed						

* in the intervention group only.

^#^ in the CAPEDP-A subsample only.

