### An ancillary study: the CAPEDP-A Study

Assessment of attachment security and caregiver behaviour being particularly complex from a procedural point of view, an ancillary study involving a subsample of the CAPEDP population was designed to investigate this particular point: the CAPEDP Attachment (CAPEDP-A) Study. The objectives of this ancillary study were to assess the impact of the CAPEDP intervention in terms of increasing infant attachment security and maternal reflexive ability and reducing infant attachment disorganisation and maternal disorganizing behaviour when the child was from 12 to 15 months old.

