#### CAPEDP-A subsample

When their child reached 12 months of age, all families participating in the main CAPEDP trial were consecutively invited to participate in the CAPEDP-A study. After receiving information about the study, and if they accepted to participate with their child, mothers signed an informed consent form and an appointment was given to them for a two hour assessment procedure within the following fortnight. Inclusion was terminated when the required 120 mothers had accepted to participate with their child. Mothers received 50 euros gratification for participating in the CAPEDP-A assessment.

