Maternal disrupting behaviour was assessed using the Atypical Maternal Behavior Instrument for Assessment and Classification (AMBIANCE) scale [58]. This 5-dimension scale, scored on the SSP procedure video, measures a broad range of maternal behaviors that can be potentially disorganizing to infants' attachment. Higher scores reflect higher levels of maternal disorganising behaviour when attachment issues are raised. The scoring team was trained by [name] and [name], the creators of the AMBIANCE scale, in a training session in Paris in 2008 and demonstrated full reliability. AMBIANCE coders were different from SSP coders and blind to the randomisation group of the families being assessed.

Parental reflexive capacity was assessed using the Insightfulness Assessment (IA) interview [59]. This is a semi-structured interview concerning the mother’s capacity to see things from the child’s point of view. It is assessed after she has viewed a video clip of herself with her child (nappy changes, free play, feeding or SSP). The IA is scored using ten sub-scales, and results in a classification into four categories. Each dyad was video-taped for SSP, nappy change, feeding and free play. The four IA raters achieved reliability on IA rating during a specific 2007 training with the team that created the instrument. Raters for IA were blind to the randomisation group of the dyad. The IA interviews took place at the same time as the SSP, when the infant was from 12 to 15 months of age.

Psychologists were asked to keep case notes on each home visit. These will be used to evaluate the frequency of the different themes that were notified as discussed during the home visit, the home visitor’s subjective perception of the visit, and the extent to which the home visitors’ preoccupations during that visit corresponded to the intended intervention.

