##### Secondary analyses

Data that are normally distributed will be analyzed using Student’s t test for continuous data, and chi-square test for categorical data, if the corresponding assumptions are fulfilled. If not, appropriate non-parametric methods will be used. In the intervention group, compliance to the CAPEDP program will be described by the proportion of planned home visits that actually took place performed reported to those scheduled. All statistical analyses will be considered significant at the 5% confidence limit using 2-sided tests. SAS software (version 9.1) will be used for statistical analyses.

More than 5,000 home visits were scheduled. A qualitative and quantitative analysis is being performed on the home visitors’ case notes to evaluate the extent to which the intended intervention program was effectively implemented or not. Case notes are analysed with regard to the frequency of themes that were declared as discussed during each home visit as well as the home visitors’ subjective perceptions of the visit.

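### Table 1 sets up AMBIANCE, a graded scale, as a categorical outcome cut at 5; with 120 dyads the score should lead and the cut support it

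*Protocol article*

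**What the plan says.** Under Procedures and outcome measures, the protocol article describes AMBIANCE as a scale with five dimensions, scored from the Strange Situation video: "Higher scores reflect higher levels of maternal disorganising behaviour when attachment issues are raised". The AMBIANCE row of Table 1 gives no score range. It labels the outcome categorical and lists two classes, "Maternal Affective Communication not Disrupted if < 5" and "Maternal Affective Communication Disrupted if ≥ 5", followed by two sub-styles.

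The sub-study objective, in the section on the CAPEDP-A Study, includes "reducing infant attachment disorganisation and maternal disorganizing behaviour when the child was from 12 to 15 months old". It names no scale of analysis.

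The only test rule that could apply is the general one under Secondary analyses: a t test for continuous, normally distributed data, "chi-square test for categorical data, if the corresponding assumptions are fulfilled", and non-parametric methods otherwise. All tests are two-sided at 5%.

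On size, the CAPEDP-A subsample section says: "Inclusion was terminated when the required 120 mothers had accepted to participate with their child". The article gives no power statement, effect size or expected disrupted rate for this outcome.

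**The concern.** A cut at 5 counts only mothers who cross it. A mother who improves but stays on the same side contributes nothing, and a mother just under 5 is treated like one at the bottom of the scale. The objective is to reduce disorganising behaviour, which can happen by degrees.

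Table 1 read together with the general test rule leads to the less efficient analysis of a score that must already exist for the cut to be applied. In a sub-study of 120 dyads this raises the chance of a false negative on one of its four objectives. A non-significant comparison of proportions could then be read as no effect on maternal behaviour.

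**Working it through.** **Check of method.** The article states no power figure for AMBIANCE, so there is none to reproduce. The three main-trial sample sizes (90% power, two-sided 5%) serve as a check: the normal-approximation formula gives 112, 98 and 188 per group, against 113, 99 and 189 stated under Determination of sample size.

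**Inputs**
- Size: 120 dyads. Randomisation in the main trial is 1:1, so 60 per arm is assumed; mothers were invited consecutively at 12 months and the split is not fixed.
- Effect: not given. The main trial's standardised effects are borrowed: CBCL 3/8.95 = 0.34, EPDS 2/4.6 = 0.43, HOME 2/4.3 = 0.47.
- Share of controls at 5 or above: not given; 30% to 70% assumed.
- Shape: a normal score shifted by the same d SD for every mother (assumed).

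**Formulas**
- Score: two-sample t test, noncentral t with 118 degrees of freedom and noncentrality d × √(60/2).
- Cut: if a share p_c of controls is disrupted, the intervention share is p_t = Φ(Φ⁻¹(p_c) − d). Power = Φ[(p_c − p_t − 1.96 × SE₀)/SE₁], where SE₀ is the pooled and SE₁ the unpooled standard error.

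**One case in full:** d = 0.335, p_c = 0.50.
- Score: noncentrality 0.335 × 5.477 = 1.84; power 44%.
- Cut: p_t = Φ(−0.335) = 0.369 and the mean proportion is 0.434. SE₀ = √(0.434 × 0.566 × 2/60) = 0.0905. SE₁ = √[(0.25 + 0.369 × 0.631)/60] = 0.0897. Power = Φ[(0.131 − 0.177)/0.0897] = 30%.
- Loss: 14 points.

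**Results, 60 per arm** (losses taken before rounding)

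| d | Power on score | Power on cut, controls 30% / 50% / 60% / 70% disrupted | Loss in points |
|---|---|---|---|
| 0.34 | 44% | 26 / 30 / 31 / 29% | 18 / 14 / 14 / 15 |
| 0.43 | 66% | 40 / 46 / 47 / 46% | 26 / 19 / 19 / 20 |
| 0.47 | 71% | 44 / 51 / 52 / 51% | 28 / 20 / 19 / 21 |

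**Sensitivity**
- With 20% of controls disrupted, the losses at the same three effects are about 22, 33 and 35 points.
- Over d from 0.2 to 0.8 and control rates from 10% to 80%, the loss runs from about 6 to 57 points.
- The effect detectable with 80% power is 0.51 SD on the score, against 0.66 SD (50% of controls disrupted) or 0.77 SD (30%) on the cut.
- A 50/70 split changes little: at d = 0.5 and 50% disrupted, 77% on the score and 56% on the cut.
- A coarse score does not rescue the cut. Simulated in whole points from 1 to 7 (an assumed range), with d = 0.5 and 50% of controls disrupted, power is 75% for the t test, 74% for the Mann-Whitney test and 58% for chi-square.
- The uniform shift matters. Suppose instead that 40% of controls score 5 or above on an assumed 1-to-7 score, and that the programme moves half of the disrupted intervention mothers to 4 and changes nobody else. Chi-square then has about 70% power, and the t and Wilcoxon tests about 20% each.

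**The case against.** The best counter-argument is that nothing assigns a test to AMBIANCE. The Table 1 column describes how instruments are built and scored, and a listed threshold is not always the analysed variable: the CBCL row carries clinical ranges and the EPDS has thresholds in the text, yet the primary analyses compare both as scores. A fuller protocol or analysis plan, not shown, may analyse the AMBIANCE score. This stands in part. A reader might infer that the plan prescribes chi-square for AMBIANCE; the article supports only the weaker statement that its label and its general rule lead there. The label still matters. The ADBB, VASQ and CBCL rows give score ranges next to their cuts, while the AMBIANCE row gives none. If a fuller plan does use the score, Table 1 misdescribes the outcome and needs the same correction.

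Second, the classification is the instrument's own, and fewer disrupted mothers would also meet the objective. That stands, and the last simulation shows that an effect confined to mothers around the cut can favour the classification. It is a reason to report both, not to leave the score out.

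Third, even the score has only 44% to 71% power under the borrowed effects. That is true: the change improves the sub-study but does not make it well powered.

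A reader might also extend the point to the Attachment Q-Sort, whose row ends with "Secure attachment if ≥0.35". The documents do not support this. That row is not labelled categorical, it lists the correlation with the secure pattern itself, and its layout matches instruments that are analysed as scores. Nor does any passage say how many Q-Sort assessments there are per arm; the 189 per group belongs to the CBCL calculation.

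**Conclusion.** The point holds at low severity, for one ancillary outcome. Table 1 types a graded scale as categorical with a cut at 5, and the general rule would then send it to the less efficient test. Under a uniform shift of 0.34 to 0.47 SD, 60 dyads per arm and 30% to 70% of controls at 5 or above, the cut costs roughly 14 to 28 points of power. All of these inputs are assumed or borrowed. A reader might take the range as a property of the trial; it is not, because the documents give no AMBIANCE effect, SD, score range or disrupted rate, and other inputs move the loss in either direction.

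**What to change.** In Table 1 and under Secondary analyses, name the AMBIANCE level score as the lead comparison for maternal disruptive behaviour. Compare it between arms with the t test, or with the Wilcoxon test if the score is coarse or skewed; the existing rule allows both. Report the mean or location difference with its confidence interval, and give disrupted versus not disrupted at 5 as a supportive result. Record the choice before any comparison by arm is seen.

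No new data, visit or rater is needed, because the score is coded before the cut is applied. The downside is that a score difference is less directly interpretable than a proportion, and an effect confined to mothers near the cut would show better on the classification. Reporting both covers this.
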